### Data management and monitoring

The patients will be identified by the patient code:
Number of the center (1 digit)Number of the patient in the center, by chronological order of selection (2 digits)First letter of first nameFirst letter of family name

#### Source documents

Source documents are original documents and patient records from which patient data are reported in the e-CRF. The investigator must commit to allow direct access to data sources in the study during inspections or audits.

The source documents that may be used to complete the e-CRF are the patient records. The investigator for each study center commits to allow direct access to the patient records during inspections or audits.

The encrypted data is transmitted to the data-management center via a secure internet connection.

The eCRF will be designed to capture all relevant medical information from patients included in the project. The study methodologist will have a restricted reader-only access to all data in order to monitor the progress and the quality of the data.

The purpose of an audit is to confirm that the study is conducted as per protocol, International Conference on Harmonisation-Good Clinical Practice (ICH-GCP), and applicable regulatory requirements; that the well-being and the rights of the subjects enrolled have been protected; and that the data relevant for the evaluation of the investigational product have been recorded, processed, and reported in compliance with the planned arrangements. The investigators will permit a direct access to all study documents, drug accountability records, medical records, and source data.

#### Data processing

Individual data needed for the study analysis must:
Be entered in the e-CRF as they are obtained, for both clinical and paraclinical dataBe anonymized by the investigatorBe authentified by an electronic signature of the investigatorAll be entered, and missing data must be justified

#### Site training and monitoring procedures

The monitor must present the protocol and all procedures related to the study during an initiation visit performed before the first patient is included. A case report form of completion guidelines will be provided to the investigator.

The monitor will be allowed to have access to all source documents needed to verify the entries on the eCRF and other protocol-related documents.

To ensure accurate, complete, and reliable data, the sponsor or its representatives will do the following:
Provide instructional material to the study sites, as appropriateProvide a start-up training session to instruct the investigator(s) and study coordinator(s). This session will give instruction on the protocol, the prompt and full completion of the clinical report forms, study procedures, and the transmission of data in a timely manner to the clinical database for statistical analysesMake periodic visits to the study siteBe available for consultation and stay in contact with the study site personnel by mail, telephone, and/or faxReview and evaluate case report form data and useConduct quality review of database

Routine monitoring visits will be made by the monitors, designated by the sponsor to check compliance with the protocol, the completeness, accuracy, and consistency of the data and adherence to Good Clinical Practice (GCP).

The principal investigator must ensure that eCRFs are completed in a timely manner and must allow periodical access to eCRFs, patient records, drug logs, and all other study-related documents and materials.

The investigator will agree to provide the monitor direct access to the subjects’ source data, which may exist in the form of hospital records, patient files and notes, and laboratory assessment reports and results.

Considering the low risks in this study, there will be no formal Data Safety and Monitoring Board for this study.

### Trial governance and monitoring

The sponsor is responsible for the administrative and financial management of the study, for its quality, and for the choice of the investigators and sites. The sponsor is also responsible in the assessment of sAE, in reporting any suspected unexpected serious adverse reaction (SUSAR) and new events according to the legislation and good clinical practices, to the competent authorities. In addition to the expedited reporting, the sponsor shall submit, once a year, throughout the clinical trial or on request, a safety report to the competent authorities and the Ethics Committee (EC) of the concerned Member States taking into account all new available safety information received during the reporting period. The aim of the annual safety report is to assess the safety conditions of subjects included in the concerned trial(s). It should be the same for the competent authorities (CA) concerned and the Ethics Committee concerned. The sponsor is responsible for the ongoing safety evaluation of the Investigational Product. The sponsor should promptly notify all concerned investigators and the regulatory authorities of findings that could affect adversely the safety of subjects, impact the conduct of the trial, or alter the CA approval/EC’s favorable opinion to continue the trial.

The investigator is responsible for the study quality, the respect of the GCP, and protocol during the conduct of the study. The investigator will ensure information on the study is given to participants and will check that they have given their informed consent. The study coordinator (psychologist in the department of the CHU Adult Psychiatry of Montpellier) will be in charge of coordinating the 9 centers: general organization (follow-up of inclusions of all centers), discussing progress, and study logistics. Each site will have a co-investigator responsible in contacting an appropriate pool of potential subjects and inviting them to participate in the study as well as ensuring the participants’ eligibility. A core project management team consisting of the principal investigator, all co-investigators, and study coordinator will meet monthly to oversee the general running of the trial.

Psychologists in each center will be in charge of assisting the investigators on site for the following:
Management of study on siteReporting of data in the eCRFVerification of respect of study proceduresRecruitments

Another psychologist, from each center, will deliver the ENERGY therapy.

The physicians will be responsible in presenting the study (information, consent, inclusion) and following the patients during the entire study. Study nurses will be responsible in the management of blood sample, freezing, and shipment.

The methodologist will be in charge of the quality of the data and the statistics.

The laboratories implicated in the study will be in charge of the reception, storage, and analysis of blood samples.

GCP requires that the clinical protocol, any protocol amendments, the informed consent and all other forms of patient information related to the study (e.g., advertisements used to recruit patients), and any other necessary documents be reviewed by an Independent Ethics Committee (IEC)/Institutional Review Board (IRB). IEC/IRB approval of the protocol, informed consent and patient information, and/or advertising, as relevant, will be obtained prior to the authorization of enrolling patients in the study. The study shall be conducted as described in this approved protocol. Any revisions/amendments to the protocol will not be permitted without prior approval by the study steering committee. Any amendments to the protocol will require IEC/IRB approval prior to implementation of any changes made to the study design.

### Statistical analysis

The statistical analysis plan (SAP), covering all the analyses to be performed on all data, will be written before database lock for final extraction.

For all collected variables, descriptive statistics will be shown for both study arms in order to verify the initial comparability of the groups. For metric variables, a check as to whether the data can be assumed to be normally distributed will be first conducted. For normally distributed variables, means and standard deviations will be calculated, whereas for skewed variables, medians and ranges will be given. For categorical variables group proportions and contingency tables will be prepared.

All tests of efficacy will be conducted on an intentions to treat (ITT) basis using, in case of missing data, the Last Observation Carried Forward method, and/or multiple or mean imputation [50]. A per protocol sensitivity analysis will also be performed taking into account only patients who completed the whole study without any major protocol deviations. This will enable us to reinforce the stability of results obtained by ITT approach.

Significance level will be set at *p* < 0.05. All statistical analyses will be performed using SAS software (SAS Institute, Cary, NC, USA).

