### Blinding

The psychologists performing inclusion, 3-month, and 9-month assessments will be blind to the allocations of the patients to either study arms of the randomized controlled study (RCT). Patients and psychologists performing the ENERGY therapy will be asked to avoid telling the assessor to which group they/the patient belongs to. A psychologist, blind to the randomization process, will perform the assessments, and another psychologist will perform the therapy interventions. Participants will be asked to not reveal their group allocation to the assessors. The data analysts that will be performing the analyses at the conclusion of the trial will also be blinded as to what group the data corresponds to. Unblinding should occur only in exceptional circumstances in case of any adverse events (AE) which will be reported immediately to the investigator.

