If a patient misses their appointment, the psychologist will call him/her. All attempts will be documented in the patient’s medical records. In case of discontinuation, the investigator will perform all examinations scheduled for the final study visit, which includes recording of AEs. In any case, the patient will be treated in accordance with standard care in the center.

Investigators should make every effort to minimize the number of patients lost to follow-up and to obtain a maximum of information on patients lost to follow-up, particularly in the search for any AEs.

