### Trial withdrawal or discontinuation

Study participation is voluntary. The subjects have the right to withdraw their consent from the study at any time and for any reason, without jeopardizing their medical care. The investigator also has the right to withdraw patients in agreement with the sponsor or his delegate. The investigator has the right to withdraw subjects from the trial in the event of concurrent illness, adverse events, and treatment failure after a prescribed procedure, protocol violations, and other reasons.

Subjects must be withdrawn from the study under the following circumstances:
The subject withdraws consent.Development of another illness or condition which would interfere with the subject’s continued participation.Discovery that the subject entered the clinical trial in violation of the protocol or occurrence of a significant protocol violation during the clinical trial.Any situation that in the opinion of the investigator would pose inacceptable risks to the subject if trial participation is continued.

For any discontinuation, the investigator should obtain all required details and should document the date and reason of the premature termination in the CRF.

If the reason for withdrawal is an AE, the specific event will be recorded in the CRF. The investigator will make thorough efforts to document the outcome.

Patients prematurely withdrawn or lost to follow-up will be analyzed at least in the safety set and in the conditions of confidentiality.

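### The protocol permits LOCF and mean imputation for the primary intention-to-treat test, names no primary missing-data method, and plans no analysis that tests the missing-data assumption

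*Protocol article*

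**What the plan says.** Under Statistical analysis, the protocol states: "All tests of efficacy will be conducted on an intentions to treat (ITT) basis", and it fills gaps by "using, in case of missing data, the Last Observation Carried Forward method, and/or multiple or mean imputation". It gives no order of preference, no rule for when each method applies and no missingness assumption. The only sensitivity analysis named there is this: "A per protocol sensitivity analysis will also be performed taking into account only patients who completed the whole study without any major protocol deviations".

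The primary comparison (Main endpoint analysis) is a t test and linear regression on the change in MFI score from inclusion to 9 months. A mixed-effects model over the three visits is planned, but only under Secondary endpoint analysis.

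Three other statements bear on how much 9-month data will be missing and who is analysed:

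- Trial withdrawal or discontinuation lists, among the reasons for mandatory withdrawal from the study, "Discovery that the subject entered the clinical trial in violation of the protocol or occurrence of a significant protocol violation during the clinical trial".
- The same section adds: "Patients prematurely withdrawn or lost to follow-up will be analyzed at least in the safety set".
- Data collection says: "In case of discontinuation, the investigator will perform all examinations scheduled for the final study visit".

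**The concern.** The primary time point is 9 months, about six months after therapy ends, and the only scheduled MFI between baseline and then is at 3 months, about the end of therapy. For a patient lost in between, LOCF treats a score taken at the end of therapy, or on leaving, as the score six months after therapy. Whether a benefit lasts that long is the question the trial asks. For a patient lost before month 3 with no later measurement, LOCF carries baseline and records no change.

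Filling gaps with a mean adds values without scatter. Depending on which mean is used, this either understates the standard error or pulls the arms together.

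The protocol expects 15–20% loss over 9 months, so the rule for these patients can affect the primary result. A per-protocol analysis of completers does not show how sensitive that result is to the missing-data assumption, because it leaves out the patients concerned. Mandatory withdrawal after a significant protocol violation adds missing 9-month values that continued follow-up could avoid.

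**Working it through.** **Inputs from the protocol (Determination of sample size and power calculation):** a 2-point effect; SD 4 in both groups at both times; alpha 0.05 (two-sided assumed); power printed as .085 and read as 0.85; 73 per group needed; 100 per group recruited; loss 15–20%.

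**Assumed, because the protocol does not give them:** between-visit correlation 0.5; data missing completely at random; the timing of losses; the size of the effect at 3 months.

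**1. The plan's own figure.** The normal approximation for a difference of 2, SD 4 and power 0.85 gives 72 per group. The t-based calculation gives 73 (power 0.851), so the stated 73 is reproduced. Allowing for loss, 73/0.85 gives 86 and 73/0.80 gives 92, so 100 is ample. With 80 to 85 completers per arm, power is about 0.885 to 0.903. The problem is validity, not lost power.

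**2. LOCF when the effect wanes.** Suppose the effect is 2 points at month 3 and 0 at month 9, with 20% lost.

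- False benefit = share of all patients lost after month 3 × 2.
- SD of change = 4 × √[2(1 − 0.5)] = 4, so SE = 4 × √(2/100) = 0.566.
- Type I error = P(Z > 1.96 − shift/SE) + P(Z < −1.96 − shift/SE).

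| Losses after month 3 | Shift | Shift/SE | Type I error |
|---|---|---|---|
| half (10% of patients) | 0.2 | 0.354 | 6.4% |
| all (20% of patients) | 0.4 | 0.707 | 10.9% |

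A three-visit simulation of the second row (3,000 trials) gave a shift of 0.41 and a rejection rate of 11.3%. The correlation matters. At 0.3 the SD of change is 4.73, the SE is 0.669, and a 0.4-point shift gives 9.2%. At 0.7 the SD is 3.10, the SE is 0.438, and the same shift gives 15.0%.

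**3. LOCF when the effect is sustained.** If the effect is 2 points at both visits and baseline is carried for all of the 20% lost, the estimate is 2 × 0.80 = 1.6. If baseline is carried for half of them, it is 2 × 0.90 = 1.8.

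**4. LOCF with no effect at any visit.** The simulated type I error is 5.0%, so LOCF's main fault is bias and not a generally inflated error rate.

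**5. Mean imputation, arm mean.** With k of n = 100 observed per arm, the ratio of apparent to true SE is √[(k − 1)/(n − 1) × k/n]. Type I error = 2 × [1 − Φ(1.96 × ratio)].

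- 15% missing (k = 85): √(84/99 × 0.85) = 0.849. Apparent SE is 0.521 against a true 0.614. Type I error is 9.6%.
- 20% missing (k = 80): √(79/99 × 0.80) = 0.799. Apparent SE is 0.505 against a true 0.632. Type I error is 11.7% (simulation 12.0%).

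The ratio, and so the type I error, does not depend on the SD or the correlation.

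**6. Mean imputation, pooled mean.** Simulation of 20,000 null trials gave a type I error of 5.2% at 15% missing and 5.0% at 20%. A true 2 points becomes 2 × 0.85 = 1.7 or 2 × 0.80 = 1.6.

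**The case against.** **The illustrations are selective.** This is partly right. The 10.9% for LOCF needs every loss to fall after month 3 and the effect to vanish completely. With half the losses after month 3 it is 6.4%. A larger transient effect would give larger figures, but the protocol hypothesises only 2 points, so nothing above that is supported. The type I inflation from mean imputation holds for the arm mean only, and the protocol does not say which mean it intends; filling unanswered questionnaire items is another possible meaning.

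**LOCF need not carry the 3-month score.** This stands. Final-visit examinations are to be done at discontinuation, so a patient who leaves at month 6 and attends would have a month-6 value. That softens the bias if an effect wanes gradually. The value is still taken before month 9.

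**A reader might infer that the withdrawal rules contradict intention to treat.** They do not. Analysis at least in the safety set is a minimum, not an exclusion, and imputing missing values presupposes that patients without a 9-month score stay in the analysis. What remains is that mandatory withdrawal creates avoidable missing data, and that neither the efficacy set for these patients nor their 9-month follow-up is stated.

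**A reader might infer that the method will be picked after seeing results.** The protocol does not show this. The SAP "will be written before database lock for final extraction", changes to the initial SAP need a protocol amendment, and "The data analysts that will be performing the analyses at the conclusion of the trial will also be blinded". A choice made after outcomes have accrued is possible, no more.

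**The choice can be left to the SAP.** The choice among sound methods could be. But the protocol itself lists two unsound ones as acceptable for the efficacy tests, and a blinded analyst who follows it would still get the biases above. Multiple imputation, also on the list, is sound if properly done.

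**Conclusion.** The point holds. Followed as written, the protocol permits a primary analysis whose estimate is biased (LOCF, pooled mean) or whose standard error is too small (arm mean), and it names no analysis that would reveal this.

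At the protocol's own loss rates and 100 per arm, the arm-mean figures of 9.6% and 11.7% and the pooled-mean shrinkage to 1.7 or 1.6 points need only the assumption that data are missing completely at random. The LOCF figures are illustrations. A false benefit of 0.2 to 0.4 points, or an estimate of 1.6 in place of 2, depends on assumed dropout timing and on whether the effect wanes; the type I errors of about 6% to 11% also depend on the assumed SD of change of 4.

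The documents do not support the stronger conclusions that every listed method inflates the type I error, that withdrawn patients are excluded from the efficacy analysis, or that the method will be chosen post hoc.

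**What to change.** 1. Delete LOCF and mean imputation from the efficacy tests.
2. Name one primary method in advance. One option is a likelihood-based repeated-measures model of the primary MFI score at 3 and 9 months, with baseline, visit, arm and arm-by-visit terms, in all randomised patients, reporting the 9-month contrast. The other is multiple imputation by arm using the 3-month value. Both assume data missing at random.
3. Add a delta-adjusted or reference-based sensitivity analysis. The per-protocol analysis can stay, but not as a check on missing data.
4. Reconcile Statistical analysis, Data collection and Trial withdrawal or discontinuation. State that patients withdrawn for protocol violations stay in the intention-to-treat set, and whether their 9-month MFI is still sought where consent allows.

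The cost is small: SAP and protocol wording, plus a short amendment on follow-up after withdrawal. A mixed-effects model over the three visits is already planned as a secondary analysis, and procedures for contacting patients already exist. The sample size does not change.

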#### Main endpoint analysis

The efficacy of the ENERGY intervention will be studied firstly by comparing the change in fatigue score (using the scores on the MFI) between inclusion/randomization and the 9-month follow-up (primary outcome) in the intervention group compared to the TAU group.

For each subject, the relative difference (delta) between the inclusion and 9-month fatigue score will be calculated. The normality of the delta score will be tested using the Shapiro Wilk’s test. If the distribution is skewed a transformation will be performed to normalize it.

Study arms will be compared between inclusion scores and the 9-month scores using mean differences. These comparisons will be done using Student’s *T* test and general linear regression models adjusting for covariates. Socio-demographic and clinical variables will be tested as potential confounders using general linear regression models, with the *p* value set at 0.10.

A second analysis will be carried out with the general fatigue score as the outcome variable, adjusting for general fatigue score at inclusion.

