### Determination of sample size and power calculation

The main objective is to evaluate the efficacy of a therapeutic protocol for the management of fatigue in schizophrenia patients. The change in fatigue level will be compared 6 months after the intervention (9-month follow-up) between two groups of patients: one following the 3-month individual program for the management of fatigue, and one receiving care as usual. The sample size calculation is based on the change in the general fatigue score, one of the five sub-scales of the Multidimensional Fatigue Inventory (MFI) [29], measured at inclusion and 9 months later.

A study exploring the psychometric properties of the MFI in 93 out-patients with schizophrenia spectrum disorders reported a mean score on the general fatigue subscale of 13.4 (standard deviation (SD): 3.9) [30]. An earlier study reported a mean score of 16 (SD 3.2) for this sub-scale in 166 patients with fibromyalgia and chronic widespread pain [49].

In our study of SZ patients attending a day hospital, with a general fatigue subscale score greater or equal to 10 at study entry, we can expect an average score of approximately 16 (SD 4) on this subscale.

We can also hypothesize a 2-point reduction in the mean score on this sub-scale between the start of the trial and the 9-month follow-up in the group receiving the intervention. No change in the severity of fatigue is expected in the group receiving treatment as usual. Under this effect-size hypothesis, with scores in both groups set at 16 (SD 4) at inclusion, the mean score in the group receiving the intervention is expected to drop to 14. Under the hypothesis of a stable standard deviation of 4 in both groups and at both time points, power set at .085 and alpha at *p* = 0.05, 73 patients per group are necessary.

In order to allow for loses at follow-up (estimated for SZ patients at 15–20% over a 9-month period), it will be necessary to recruit 100 subjects per group.

The 9 centers participating in this study are part of the French network of expert centers in schizophrenia of the FondaMental foundation. Participants will be recruited directly from the day hospitals in each of the centers.

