#### Secondary endpoint analysis

The secondary outcome analyses will be assessed similarly to the main endpoint analyses. Specifically, for normally distributed variables, means and standard deviations will be used to conduct the analyses, whereas for skewed variables, medians and ranges will be used.
A secondary outcome variable will be constructed, measuring the change in fatigue score (based on MFI scores) between inclusion scores and the 3-month follow-up, representing the end of the ENERGY intervention (for the intervention study arm). Change in fatigue score over the three time points using mean differences in scores between the intervention and TAU study arms will be compared using a mixed-effects model, taking into account the repeated and reversible time-dependent outcome measures.Assessment of the effect of the intervention on a range of exploratory outcomes (clinical and cognitive factors, biological markers) measured at the 9-month follow-up will be carried out using either linear regression models or logistic regression models, depending on the type of variable (continuous or binary). These scores will be compared to the initial scores obtained at inclusion. For each outcome variable, the model will be adjusted for the baseline value. These secondary analyses will include measures of:

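### The primary fatigue variable is called a relative difference but sized as an absolute 2-point drop, and the model that names baseline fatigue is placed second

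*Protocol article*

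**What the plan says.** **Main endpoint analysis.** The per-patient variable is introduced as follows: "the relative difference (delta) between the inclusion and 9-month fatigue score will be calculated". No formula or denominator is given. Its normality is checked by Shapiro-Wilk, and "If the distribution is skewed a transformation will be performed to normalize it"; the transformation is not named. The arm comparison is then put in absolute language: "Study arms will be compared between inclusion scores and the 9-month scores using mean differences". On method: "These comparisons will be done using Student’s *T* test and general linear regression models adjusting for covariates". On covariates: "Socio-demographic and clinical variables will be tested as potential confounders using general linear regression models, with the *p* value set at 0.10". Listed second is a model with the general fatigue score as outcome, "adjusting for general fatigue score at inclusion".

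**Secondary endpoint analysis.** For the exploratory 9-month outcomes: "For each outcome variable, the model will be adjusted for the baseline value".

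**Determination of sample size and power calculation.** Sizing is said to rest on change in the general fatigue subscale, with a mean falling from 16 to 14 under the intervention and no change under usual care. "Under the hypothesis of a stable standard deviation of 4 in both groups and at both time points, power set at .085", with alpha 0.05, leads to 73 per group. Recruitment is 100 per group, to cover 15–20% loss.

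**Primary outcome measures** names the MFI score without choosing a subscale or total.

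**The concern.** Three things about the primary analysis are left in conflict.

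- **Scale.** A relative difference, read literally, is not the quantity the trial was sized on. A 2-point drop is 20% of the entry floor of 10 and 12.5% of the planning mean of 16. An unnamed, data-triggered transformation could move the reported effect further from points.
- **Model.** A t-test, a regression with data-selected covariates and a baseline-adjusted model all appear. The only one that names baseline fatigue comes second, although the exploratory 9-month outcomes are explicitly adjusted for baseline.
- **Variance.** The sizing refers to change but uses the SD of a single score. Whether 73 per group gives the intended power for a change-score test depends on a correlation that is not given.

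At stake are an efficacy estimate that may not be comparable with the 2-point planning effect, a choice between models that the article leaves open, and power given up although the data needed to recover it are already collected.

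**Working it through.** **Inputs from the sample size section.** Difference 2 points; SD 4 in both arms at both times; alpha 0.05 (taken as two-sided; the article does not say); 73 per group; 100 recruited per group; loss 15–20%.

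**Assumption.** r, the correlation between inclusion and 9-month scores, is not in the document, so a range is used. The only related figure is the MFI test–retest correlation of .66 to .91 under Primary outcome measures. Its interval is not given, and a 9-month correlation may be lower.

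**Step 1: reproduce 73.** Normal approximation: n = 2(1.960 + 1.036)² × 4² / 2² = 2 × 8.978 × 4 = 71.8, so 72 per group. The exact noncentral t calculation gives 73 (power 85.1% at 73, 84.6% at 72). Power 0.80 would give 63 and 0.90 would give 85 by the normal approximation. The intended power is therefore 0.85, and .085 is a misprint that does not affect the sample size.

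**Step 2: allow for loss.** 73/0.85 = 85.9, so 86; 73/0.80 = 91.25, so 92. Both are below 100. Of 100 recruited, 80 to 85 per arm are expected to be evaluable.

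**Step 3: SD of each analysed variable.**

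- Change score: variance = 16 + 16 − 2r × 16 = 32(1 − r), so SD = 4√(2(1 − r)). This equals 4 only when r = 0.5.
- Baseline-adjusted 9-month score: residual SD = 4√(1 − r²).
- Since 2(1 − r) − (1 − r²) = (1 − r)² ≥ 0, the adjusted variance is never the larger.

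**Step 4: power for 2 points** (noncentral t; one fewer degree of freedom for the adjusted model).

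| r | SD change | SD adjusted | 73/arm: change v adjusted | 80/arm: change v adjusted | n/arm for 85%: change v adjusted |
|---|---|---|---|---|---|
| 0.3 | 4.73 | 3.82 | 71.8% v 88.2% | 75.7% v 90.9% | 102 v 67 |
| 0.5 | 4.00 | 3.46 | 85.1% v 93.4% | 88.2% v 95.2% | 73 v 55 |
| 0.66 | 3.30 | 3.01 | 95.3% v 97.9% | 96.8% v 98.7% | 50 v 42 |
| 0.8 | 2.53 | 2.40 | 99.7% v 99.9% | 99.9% v 99.9% | 30 v 27 |

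At r = 0.45 with 80 per arm, the change SD is 4.20 and power is 85.0%. At r = 0 the adjusted model still has 85.1% power with 73 per arm, so 73 is enough for it at any non-negative r.

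**Step 5: if *relative* did mean percent change.** In a simulation with 73 per arm, entry score at least 10 and scores bounded at 4–20 (an assumed range), a t-test on percent change had power 72.8%, 83.9% and 94.3% at r = 0.3, 0.5 and 0.66. The adjusted model had 87.6%, 91.6% and 97.2%.

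**The case against.** Several stronger readings are tempting, and the document does not support them.

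- **That the endpoint is a percentage change.** A reader might infer this from *relative*. With no formula, and with the same section speaking of change in score and mean differences, it is only one reading. What stands is that the term is undefined and conflicts with its surroundings.
- **That the primary test is only an unadjusted t-test.** The same sentence adds covariate-adjusted regression, and a screened clinical variable could turn out to be baseline fatigue. What stands is that baseline fatigue is not named there.
- **That the trial is underpowered.** The shortfall exists only for the change test at low r. At r = 0.66 that test has over 95% power even with 73 per arm, and 80 to 85 per arm are expected. Nothing in the document establishes r = 0.3.
- **That every secondary analysis is baseline-adjusted.** The stated adjustment is attached to the exploratory 9-month outcomes. The 3-month change and the mixed model carry no such statement.
- **That the transformation rule would usually fire.** No reliable rate can be given. The objection to the rule is that the scale would depend on the data, whatever the frequency.

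It is also fair to say that a change-score t-test is valid in a randomised trial, that the baseline-adjusted model is already planned, and that a statistical analysis plan is promised before database lock. Leaving a formula or covariate list to that plan would be no fault. But the article does not stay silent: it states a variable, a transformation rule, a covariate screen and an order of analyses, and these conflict with its own sizing.

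**Conclusion.** The point holds as an inconsistency in the primary variable and an avoidable ordering of models. It does not show that the sample size is wrong. The description of the primary variable must be reconciled with the absolute 2-point sizing, and one model should carry the efficacy conclusion.

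The gain from making the baseline-adjusted model primary depends on r: about 16 percentage points of power at r = 0.3, 8 at r = 0.5 and under 3 at r = 0.66, with 73 evaluable per arm. These figures assume a 2-point effect, SD 4 at both times and two-sided 5% alpha. The adjusted model removes the dependence on an unstated r, since the planned number suffices for it throughout the range.

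Promoting it also requires a decision on the outcome. The second analysis is on general fatigue, while Primary outcome measures and the first analysis refer only to MFI scores. The misprinted power is a minor correction.

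**What to change.** 1. Name one primary model: the 9-month fatigue score regressed on arm, inclusion score and centre (the stratification factor under Randomization and matching). Report the adjusted mean difference in points with a 95% CI.
2. State that the primary score is the general fatigue subscale on which the trial is sized, and bring Primary outcome measures, the sample size section and Main endpoint analysis into line.
3. Delete *relative*, the Shapiro-Wilk/transformation rule and the p = 0.10 covariate screen from the primary analysis. Keep the unadjusted absolute change as supportive.
4. Print power as 0.85. State that 73 per group assumes an SD of 4 for the analysed variable (r = 0.5 for a change score), which is conservative under the adjusted model.

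**Cost.** An amendment to the wording of the protocol and analysis plan, with the steering committee and ethics approvals described under Trial governance and monitoring. Item 2 is an endpoint decision and should be made before database lock. Inclusion MFI scores and centre are already collected; no new data and no change in sample size are needed.
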